## Abstract

**Background:**

Malignant pleural effusion (MPE) is a debilitating condition as it commonly causes disabling breathlessness and impairs quality of life (QoL). Indwelling pleural catheter (IPC) offers an effective alternative for the management of MPE. However, IPC-related infections remain a significant concern and there are currently no long-term strategies for their prevention. The Australasian Malignant PLeural Effusion (AMPLE)-4 trial is a multicentre randomised trial that evaluates the use of topical mupirocin prophylaxis (*vs* no mupirocin) to reduce catheter-related infections in patients with MPE treated with an IPC.

**Methods:**

A pragmatic, multi-centre, open-labelled, randomised trial. Eligible patients with MPE and an IPC will be randomised 1:1 to either regular topical mupirocin prophylaxis or no mupirocin (standard care). For the interventional arm, topical mupirocin will be applied around the IPC exit-site after each drainage, at least twice weekly. Weekly follow-up via phone calls or in person will be conducted for up to 6 months. The primary outcome is the percentage of patients who develop an IPC-related (pleural, skin, or tract) infection between the time of catheter insertion and end of follow-up period. Secondary outcomes include analyses of infection (types and episodes), hospitalisation days, health economics, adverse events, and survival. Subject to interim analyses, the trial will recruit up to 418 participants.

**Discussion:**

Results from this trial will determine the efficacy of mupirocin prophylaxis in patients who require IPC for MPE. It will provide data on infection rates, microbiology, and potentially infection pathways associated with IPC-related infections.

**Ethics and dissemination:**

Sir Charles Gairdner and Osborne Park Health Care Group Human Research Ethics Committee has approved the study (RGS0000005920). Results will be published in peer-reviewed journals and presented at scientific conferences.

**Trial registration:**

Australia New Zealand Clinical Trial Registry ACTRN12623000253606. Registered on 9 March 2023.

**Supplementary Information:**

The online version contains supplementary material available at 10.1186/s13063-024-08065-1.

## Background

Malignant pleural effusion (MPE) is a significant healthcare problem [1]. It is a common complication of advanced cancer, most frequently in lung and breast cancers [2, 3], and its presence usually signifies incurable metastatic disease. The prognosis of patients with MPE is poor, with a median life expectancy ranging from 4 to 12 months [4], and the management of MPE remains palliative in nature. MPE causes disabling breathlessness that is debilitating and is associated with poor quality of life (QoL). Therefore, the primary goal of therapy is to provide effective control of symptoms with minimal interventions.

Indwelling pleural catheter (IPC) is an ambulatory drainage device for MPE patients that permits fluid evacuation at home, avoiding hospital visits. Multiple randomised studies have proven that IPC is significantly superior to conventional talc slurry pleurodesis for the management of MPE in reducing the need for further invasive pleural interventions and hospitalisation days while providing equivalent benefits in relieving breathlessness and QoL [5–7]. IPC is now established as one of the first-line management options for MPE in recent guidelines [8, 9].

Despite the advantages of IPC, there exists a 10–20% associated complication rate [10], with IPC-related infection being clinicians’ biggest hesitation in adopting IPC use. IPC-related infections usually develop after 6 weeks post-insertion [11] and include infections of the pleural cavity/fluid, catheter tract (i.e. tunnel infections), and skin at the exit-site (i.e. cellulitis). The incidences of IPC-related infections varied among studies and was reported to be as high as 25% [7]. The largest multi-centre study and a recent review of IPC-related pleural infections found *Staphylococcus aureus* as the most common causative organism [12, 13].

IPCs share many similarities with peritoneal dialysis (PD) catheters which are also frequently complicated by peritonitis and exit-site infections (ESIs). The use of topical antibiotics (especially mupirocin) to reduce PD-related infections have been a subject of several recent studies. Mupirocin is a topical antibiotic with excellent activity against gram-positive organisms and is an attractive prophylactic option for *S. aureus*-related infections [14].

Several studies demonstrated significant reduction in peritonitis and ESIs attributed to *S. aureus* or Gram-positive organisms when mupirocin was applied around the catheter exit site [15–19]. A meta-analysis [20] also found that mupirocin prophylaxis reduced the rate of *S. aureus* peritonitis and ESIs by 66% and 62% respectively. In a prospective controlled study [21], mupirocin reduced the overall incidence of peritonitis by 61% and ESI by 55%. Specifically, *S. aureus* peritonitis was cut by 100% and ESI by 65%. The International Society for Peritoneal Dialysis (ISPD) guidelines now recommend a daily application of topical mupirocin around the catheter exit-site as prophylaxis for peritoneal dialysis patients [22, 23].

To date, no long-term preventative approaches exist for IPC-related infections, which are significant events to cancer patients and delay oncologic treatments. Management of infection requires hospitalisations with associated costs. Having a prophylactic antibiotic to reduce/prevent infection is an attractive option, but whether the use of mupirocin prophylaxis can be extrapolated to IPC infections is unknown. Patients undergoing PD and those with MPE differ in underlying comorbidities and frequencies of fluid exchanges/drainages and are exposed to different sources of infection. Results of mupirocin use in PD cannot be directly extrapolated to MPE patients with an IPC without a randomised clinical trial. Our pilot study [24] established the safety and feasibility of mupirocin prophylaxis in patients with malignant effusions, and the AMPLE-4 trial represents the next step to investigate the efficacy.

## Methods

### Study design

The Australasian Malignant PLeural Effusion (AMPLE)-4 trial is a pragmatic, multi-centre, open-labelled, 1:1 randomised study to evaluate the use of regular prophylactic topical mupirocin (*vs* no mupirocin) to reduce catheter-related infections in patients fitted with an IPC for MPE.

### Study setting

This trial will be conducted at tertiary centres across Australia, New Zealand, and Asia, and new enrolling sites will be updated regularly on the trial registration website (URL: https://www.australianclinicaltrials.gov.au/anzctr/trial/ACTRN12623000253606). This trial will include 418 patients with MPEs, who require an IPC randomised 1:1 to either topical mupirocin or no topical mupirocin (standard care) (Fig. 1).

**Fig. 1 Fig1:**
[figure not shown]
Study flow chart. ECOG, Eastern Cooperative Oncology Group; IPC, indwelling pleural catheter; MPE, malignant pleural effusion

### Participant screening, selection, and recruitment

The site principal investigator or designated site research staff will screen patients with symptomatic MPE for when an IPC is planned for treatment. Potential participants will be approached about the study and be provided with the participant information and consent form to read and to ask questions to the study team. They will also be given time to discuss the study with family and carers and their general practitioner, if needed. Eligible participants will be offered trial entry and will be enrolled after providing informed consent. The site principal investigator will be aware of their dual role as the patients’ primary physician and as a clinical researcher and where this patient dependency can be a potential conflict. Enrolment and screening logs will be maintained.

### Inclusion criteria

Patients who require insertion of an IPC for control of MPE can be considered for inclusion. MPE is defined if cancer cells are identified in the pleural fluid or pleural biopsy or is a large exudative effusion without other causes in a patient with advanced disseminated malignancy.

### Exclusion criteria

Exclusion criteria includes age < 18 years, allergy to mupirocin, ipsilateral pleural infection within past 3 months, and inability to consent or comply with the protocol.

### Treatment

#### Topical mupirocin arm

For those assigned to the topical mupirocin (interventional) arm, topical mupirocin 2% (cream or ointment) will be applied around the exit-site of the IPC for an area approximately 3 cm in diameter. An information sheet with a picture of how to apply mupirocin will be provided to patients/carers. The antibiotic should be applied within 48 h of IPC insertion and thereafter following each drainage but at least twice weekly (with dressing change) until IPC is removed or the end of this study.

#### No topical mupirocin (standard care) arm

Patients assigned to the standard care arm will be managed in the conventional manner with the usual education and care of the IPC and without topical mupirocin prophylaxis.

### Clinical care

Participants in both arms will be managed by their own clinical teams and receive all other medical treatments (including chemotherapy and radiotherapy) as deemed clinically appropriate. Patients’ medical care, including IPC care and oncology management, will be directed by their attending physicians, as per standard practice in the treatment hospital, regardless of study group allocation. This includes the frequency of drainage, drainage device (suction bottle or drainage bag), and administration of talc pleurodesis via IPC. All patients will receive standard education on IPC aftercare, have access to support services (e.g. direct phone line), and receive usual care from their attending physicians. Decision of IPC removal is made by the physicians in-charge.

### Monitoring and follow-up

Potential participants, as part of the informed consent process, will have the study procedures and follow-up plan discussed in detail.

All patients (or their carers/nurses) will be contacted by phone every week to assess for clinical outcomes, compliance, or adverse events until death or end of 6-month follow-up period (Table 1). Frequency of the phone review will decrease to monthly once the IPC is removed. If the patient is attending hospital visits for other reasons, then the telephone review may be replaced by face-to-face assessment.

**Table 1 Tab1:** Schedule of treatment for each visit and follow-up procedures

	**Study period**			
	**Pre-procedure**		**Post-procedure**	
	**Enrolment**	**Index procedure**	**Days post-procedure**	**Week**^**a**^
**Timepoint**	***Baseline***	***D0***	***D1***** ± *****24 h***	***1–24***
**Enrolment:**				
**Informed consent**	X			
**Baseline data collection**	X			
**Randomisation**	X			
**IPC insertion**		X		
**Interventions**				
**Dressing change ± mupirocin application**			X	X
**Assessments:**				
**Phone call/clinic visit**				X
**Adverse event review**			X	X
**Evaluation of exit-site**			X	X

^a^Weekly follow-up for up to 6 months (monthly if IPC is removed); *IPC*, indwelling pleural catheter

Where participants do not answer follow-up calls/attend planned study visits, the research staff will contact them again or book an additional visit if required. If the patient is an inpatient, the visit will be carried out in the hospital, if appropriate.

### Outcomes

Data on primary and secondary endpoints will be captured weekly (monthly if IPC is removed) from catheter insertion until death or end of 6-month follow-up period. Outcomes will be reported as mean or median, as appropriate.

### Primary endpoint

The primary outcome is the percentage of patients who developed an IPC-related infection from catheter insertion until death or end of 6-month follow-up period. IPC-related infection can be any one of the following:Pleural infection: presence of pus and/or bacteria (by Gram stain or culture) in pleural fluid plus a clinical picture compatible with infection (e.g. fever, leucocytosis, raised inflammatory markers).Catheter tract infection: signs of inflammation along the tract usually with swelling and significant tenderness plus a clinical presentation compatible with infection.Cellulitis at exit-site: signs of inflammation clinically warranting systemic antibiotic treatment as determined by the attending physician.

### Secondary endpoints

Infection will be analysed:As the total number of episodes for all patients in each group;As percentage of patients and as total number of episodes—each adjusted for number of days IPC is in situ for each patient;As each of the individual types of infection;Time to first episode of infection; andFor organism(s) causing infection (e.g. *S. aureus **vs *others)Hospital days will be analysed:As total days in hospital (for any reasons)As days related to IPC-related infections, similar to methods used in prior AMPLE trials [6, 25]. All records of hospitalisation will be reviewed by an independent investigator.Adverse and serious adverse events will be recorded as in previous AMPLE trials [6, 25]. Definitions for adverse and serious adverse events are listed under adverse events section in the protocol.Resources used associated with antibiotics use and IPC-related infections will be obtained from discharge letters and hospital in-patient enquiry coding. In-/out-patient management of any related complications will be captured from hospital records or self-reports from patients and will include treatments, imaging, and other interventions related to the adverse events. An experienced health economist will oversee this study aspect.Survival will be measured from randomisation to death or end of study follow-up.

### Sample size

This study will enrol 418 patients to detect a difference in IPC-related infection rate between the treatment arms. The difference that we wish to detect is 10% in the topical mupirocin prophylaxis arm (i.e. a relative reduction in infection rates of 50%) *vs* 20% in the no topical mupirocin prophylaxis (standard care) arm (based on previous studies) [7, 15–18, 25]. Previous randomised clinical trials (RCTs) reported a pleural infection rate of ~ 10% [7, 25]. Incidences of tract infection and cellulitis (combined) are often similar to the pleural infection rates in published papers. Hence, we estimated a 20% incidence for overall IPC-related infections. In the RCTs investigating mupirocin prophylaxis in PD patients, a two-third reduction in infection rates (*vs* control arms) were commonly reported [15–17]. To be conservative, we therefore estimated an incidence of 10% in our treatment arm. The sample size calculation was carried out using an anticipated chi square test to compare these proportions, assuming a 5% significance level and a power of 80%. To achieve this, we would need 199 patients per group (with an additional 5% to allow for dropouts based on previous AMPLE trial [6]), giving a total of 418 patients.

### Randomisation

Participants will be randomised 1:1 to either topical mupirocin or no topical mupirocin (standard care). Randomisation will include minimisation for (i) cancer type (mesothelioma *vs* non-mesothelioma), (ii) known presence of trapped lung (*vs* not), (iii) ECOG performance status (≤ 2 *vs* ≥ 3), and (iv) current immunosuppression (or chemotherapy) *vs* not. The Griffith Randomisation Service by the Griffith University, Queensland, Australia, provides the randomisation setup via their automated web portal. The site principal investigator or designated site research staff screening patients will be able to generate the allocation sequence using the automated centralised randomisation system, enrol participants, and assign participants to interventions based on the randomisation.

### Data management and safety

All procedures for the handling and analysis of data will be conducted using GCP ICH guidelines and the National Statement on Ethical Conduct in Human Research (2007) – *Updated 2018* and in accordance with local policies and procedures.

Patient privacy and confidentiality will be maintained, as any information that identifies participants will be available only at the enrolment study site and only to designated study investigators, all of whom will either have signed a confidentiality agreement or be employees of the hospital.

Data collected will be stored in line with the Australian Code for the Responsible Conduct of Research for clinical trials and local policy guidelines for research data archiving. Access to the final trial dataset will only be available to the research team at the lead site.

Audits, if any, are usually carried out by an independent compliance monitoring officer.

### Statistical plan

Data will be analysed on an intention-to-treat basis and per protocol basis. All participants, excluding those who withdrew prior to the randomisation intervention, will be included in the intention-to-treat analyses and analysed according to their randomised assignment. Per-protocol analyses will be performed in participants who have had at least one week of mupirocin application *vs* those who did not have any. Sensitivity analysis, e.g. with multiple imputation, will be carried out whenever appropriate, to account for missing data. The primary outcome will be analysed using chi-square test and subsequent logistic regression analyses allowing adjustments for minimisation variables. A secondary analysis of the primary outcome will utilise the time to event data, where cumulative incidence plots will be presented, and the log-rank statistic used to compare the treatment groups. In addition, Cox regression models will be used to calculate cause specific hazard ratios adjusted for minimisation variables. A competing risk analysis will also be performed to account for the competing risk of death in estimation of event rates. For binary or continuous secondary outcomes, inter-group differences will be examined using chi-square tests or two sample *t*-tests respectively, with additional logistic and linear regression analyses adjusting for minimisation variables. Adverse and serious adverse events will be reported in descriptive figures. Data analysts will be masked to the assigned groups, where appropriate.

An interim analysis is planned after 100 patients have been enrolled and completed follow-up. The purpose is to (i) assess the rate of recruitment and determine the feasibility of fulfilling the enrolment target and (ii) futility—observe the actual incidence of event rates in the control group to ensure the study is adequately powered to detect a clinically meaningful difference. We would determine if the conditional power based on the trend observed at the interim analysis decreases to less than 0.2. The need for further interim analysis will be assessed accordingly, and any decision to terminate the trial will be made by the trial steering committee.

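### The per-protocol groups are set by mupirocin received rather than within randomised arms, and the one-week threshold hardly isolates the effect of adhering

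*Protocol article*

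**What the plan says.** The Statistical plan opens with "Data will be analysed on an intention-to-treat basis and per protocol basis" and does not rank the two. For intention to treat, participants "will be included in the intention-to-treat analyses and analysed according to their randomised assignment". The per-protocol rule comes next: "Per-protocol analyses will be performed in participants who have had at least one week of mupirocin application", set against "those who did not have any". It does not mention the randomised arm and gives no further adherence criterion.

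The assigned regimen, in the section on the topical mupirocin arm, is far longer than a week. Application starts within 48 hours of insertion and then continues "following each drainage but at least twice weekly (with dressing change) until IPC is removed or the end of this study". Table 1 schedules weeks 1 to 24, and follow-up is described as six months.

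Under Monitoring and follow-up, weekly calls are made "to assess for clinical outcomes, compliance, or adverse events until death or end of 6-month follow-up period", dropping to monthly once the catheter is out. Adherence is therefore recorded weekly for as long as the regimen applies.

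**The concern.** A per-protocol analysis is meant to ask what happens when patients follow the regimen they were assigned. As worded, this rule falls short in three ways.

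- **Grouping.** Sorting by exposure alone lets patients change sides. In an open-label trial, crossover is possible in either direction. Those who never start, or who obtain mupirocin outside their assignment, may differ in prognosis.
- **Entry condition.** The treated group must have lived and used mupirocin for a week. The comparator is counted from day 0 with no such condition, which is immortal time on one side.
- **Threshold.** The Background says that catheter infections mostly appear later than six weeks after insertion. A patient who stops on day 8 and keeps the catheter goes unprotected through that period, yet counts as treated per protocol.

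Because the two analyses are listed side by side, a reader may take this result as confirming or contradicting intention to treat when it does neither cleanly.

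**Working it through.** **Inputs from the protocol article.** Rates of 20% (control) and 10% (mupirocin), 5% significance, 80% power, 199 per group and 418 in total (Sample size); 24 scheduled weeks (Table 1) or six months, about 26 weeks; median survival 4 to 12 months (Background). Two-sided testing is assumed.

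**The plan's own figure.** With pooled variance, n = [1.960 × √(2 × 0.15 × 0.85) + 0.842 × √(0.20 × 0.80 + 0.10 × 0.90)]² / 0.10² = (0.990 + 0.421)² / 0.01 ≈ 199 per group. Then 199 × 1.05 = 208.95, so 209 per arm and 418 in total. The figure reproduces, and it does not depend on the per-protocol set.

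**1. Grouping.** No non-starter rate is given. Assume 5% of 209, about 10 patients. The comparator becomes 209 + 10 = 219.
- Non-starter risk 20%: comparator stays at 20%.
- Non-starter risk 40%: (209 × 0.20 + 10 × 0.40) / 219 = 45.8 / 219 = 20.9%.
- Non-starter risk 10%: (41.8 + 1.0) / 219 = 19.5%.

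The shift is below 1 point at this level of non-starting. It grows with more non-starters or crossovers.

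**2. One-sided first week.** Assume constant hazards, no treatment effect and 20% infected by week 24.
- Week-1 deaths: 1 − 0.5^(1/17.4) = 3.9% at median 4 months (17.4 weeks); 1 − 0.5^(1/52.2) = 1.3% at median 12 months (52.2 weeks).
- Week-1 infections: 0.9% ignoring death; 1.1% (12 months) to 1.5% (4 months) with death as a competing event.
- Drop all week-1 events from the treated group only: (0.200 − 0.009) / (1 − 0.009) = 19.3% ignoring death; (0.200 − 0.0109) / (1 − 0.0240) = 19.4% at 12 months; (0.200 − 0.0146) / (1 − 0.0534) = 19.6% at 4 months.
- Drop only week-1 deaths: 0.200 / (1 − 0.0131) = 20.3% at 12 months; 0.200 / (1 − 0.0388) = 20.8% at 4 months.

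The distortion runs from about −0.7 to +0.8 points. Constant hazards probably overstate week-1 infections, given their late timing.

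**3. Threshold as a share of the course.** 1/26 = 3.8%; 1/24 = 4.2%; 1/16 = 6.3%; 1/12 = 8.3%; 1/8 = 12.5%. About 4% is the minimum, reached only if the catheter stays in throughout.

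**4. Dilution left in the set.** Assume a share q stop after about a week and revert to 20%. The treated rate is 0.10(1 − q) + 0.20q. Power is against 20% with 199 per group.

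| q | Treated rate | Power |
|---|---|---|
| 0 | 10% | 80% |
| 10% | 11% | 70% |
| 20% | 12% | 59% |
| 30% | 13% | 47% |

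At q = 30% with 5% non-starters at 20%, the intention-to-treat rate is 0.95 × 13% + 0.05 × 20% = 13.35%. The per-protocol set gives 13%. Against 10% under adherence, it removes 13.35 − 13.00 = 0.35 of 3.35 points of dilution, about a tenth.

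**The case against.** The strongest reply is that the rule is called per protocol, follows a sentence about randomised assignment, and belongs to a trial whose control is no mupirocin. A natural reading is mupirocin-arm patients with at least a week against control patients with none, and an unseen analysis plan may say so. This stands in part: the document does not state that patients will be moved between groups, and it would be wrong to report that as the sponsor's declared intention. But the article states a rule, the rule omits the arm, and the preceding sentence shows that the arm can be specified. Followed literally, it sorts by exposure.

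Several stronger readings are tempting and are not supported.

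- **That immortal time materially favours mupirocin.** The effect is under about 1 point. Excluding early infections lowers the treated rate, while excluding early deaths raises it.
- **That every included patient may have had only 4% of the course.** That is a floor. The course ends with catheter removal, and a week is then a larger share.
- **That the set will be diluted to 13%.** The 30% stopping rate is an assumption with no source in the document.
- **That a strict adherence cut-off, say 80% of weeks, would cure the problem.** It would select on behaviour after the landmark in one arm only, and infection or decline can themselves affect that behaviour. A lenient threshold does keep more of the randomised patients.

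Any per-protocol set gives up some of the protection of randomisation. What is avoidable here is giving up the arm as well.

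**Conclusion.** The concern holds for the per-protocol analysis only. As written, the comparison is as-treated, its entry condition falls on one group, and its threshold keeps early stoppers in the treated group.

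The first two faults are small in size: under 1 point for about 10 non-starters at risks of 10% to 40%, and under about 1 point for the first week under constant hazards. The threshold is the weightier fault. It leaves the set close to intention to treat wherever non-adherence consists mainly of stopping after the first week. How much that matters depends on the actual stopping rate, which the document does not give.

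A reader might infer that the primary comparison or the sample size is compromised. Neither is: intention to treat follows randomised assignment, and the 418 does not rest on this set. The point should be corrected but does not threaten the main result.

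**What to change.** 1. Define the per-protocol set within randomised arms: mupirocin-arm patients with at least one week of application, and control-arm patients with no mupirocin.
2. Start both arms at the same day-7 landmark, restricted to patients who are alive, with the catheter in place and no earlier infection. Because the first application may come up to 48 hours after insertion, state how a week of application is counted at that landmark.
3. To estimate the effect of adhering, add an analysis that censors patients when they deviate from the assigned regimen, with inverse-probability weights built from the weekly compliance data. Use this rather than a fixed percentage cut-off applied to one arm. It relies on the predictors of deviation having been measured, which should be stated.
4. Label these analyses as supportive to intention to treat.

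The cost is a wording change and some extra analysis work. Compliance is already collected, and neither the sample size nor patient care changes. Under the constant-hazard assumptions above, week-1 deaths and infections would remove about 2.4% to 5.3% of each arm from the landmark set (5 to 11 of 209), including 2 or 3 infections, plus any early catheter removals. The change should be made before unmasked data are analysed.

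### Allocation is minimised on four factors but an unadjusted chi-square leads the primary analysis; the adjusted model already planned should be the single primary analysis, for a gain that is small and conditional

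*Protocol article*

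**What the plan says.** All references are to the protocol article.

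- **Randomisation:** allocation is 1:1 and constrained: "Randomisation will include minimisation for (i) cancer type" and three further binary factors, namely known trapped lung, ECOG status (2 or below versus 3 or above) and current immunosuppression or chemotherapy.
- **Sample size:** the trial is sized on an unadjusted comparison: "The sample size calculation was carried out using an anticipated chi square test to compare these proportions". The target is 20% infected under standard care against 10% with mupirocin.
- **Statistical plan:** "The primary outcome will be analysed using chi-square test and subsequent logistic regression analyses allowing adjustments for minimisation variables". The next sentence labels the time-to-event work as secondary. No comparable label separates the chi-square from the logistic regression.

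The article does not say whether, or how strongly, the four factors predict catheter-related infection.

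**The concern.** Minimisation removes most of the chance imbalance between arms on the four factors. The variance behind an unadjusted chi-square still allows for that imbalance. If the factors predict infection, the variance is too large for the design actually used. The test then rejects less often than its nominal level, some power is lost, and a standard unadjusted interval would be wider than it needs to be. Analysing by the factors used for allocation corrects this.

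There is also a question of hierarchy. Two tests of one outcome are listed in sequence, and they can fall on opposite sides of 0.05. Without a stated rule, a borderline result could be read either way.

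Finally, the logistic model returns a conditional odds ratio, whereas the trial was sized on a difference in percentages.

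**Working it through.** **Inputs from the article**

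- Control risk 0.20: "Hence, we estimated a 20% incidence for overall IPC-related infections".
- Mupirocin risk 0.10: "we therefore estimated an incidence of 10% in our treatment arm".
- Significance level 5%, power 80%. Sidedness is not stated; two-sided is assumed because it reproduces the stated figure.
- 199 per group, 418 in total with 5% for dropout; 1:1 allocation; four binary minimisation factors.

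**Assumptions, not in the article**

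- Factor prevalences 25%, 25%, 20% and 50%, independent of each other.
- The same odds ratio for infection for each factor, varied from 1 to 3.
- Minimisation with a 0.8 biased coin.

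**Step 1. Reproduce the plan's figure.** With pooled variance and no continuity correction:

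n = [1.96 × √(2 × 0.15 × 0.85) + 0.8416 × √(0.20 × 0.80 + 0.10 × 0.90)]² / 0.10²
= [0.9897 + 0.4208]² / 0.01 ≈ 199 per group.

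Power at 199 per group is 0.800, and 2 × 199 × 1.05 = 417.9, so 418. The stated sample size is correct for a chi-square test.

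**Step 2. Direction and rough size.** Let R² be the share of outcome variance explained by the balanced factors (assumed). The true variance of the difference shrinks by about (1 − R²), but the chi-square does not use this.

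- Type I error of the chi-square: 2 × [1 − Φ(1.96/√(1 − R²))] = 4.4% at R² = 0.05 and 3.9% at R² = 0.10.
- Power of the chi-square: Φ((2.80 − 1.96)/√(1 − R²)) = 80.6% and 81.2%.
- Power of the adjusted test: Φ(2.80/√(1 − R²) − 1.96) = about 82% and 84%.

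The gain is therefore about 1.4 and 2.7 points. The chi-square's own power also rises above 80% when minimisation balances prognostic factors, so it is the right comparator, not the planned 80%.

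**Step 3. Simulation of this design.** 398 analysed patients; marginal risks 20%/10% for power and 20%/20% for type I error; 12,000 trials per setting. The adjusted test is the Wald test for treatment in the logistic model with all four factors. Monte Carlo standard error is about 0.4 points for power and 0.2 points for type I error. The last column comes from a separate run of 6,000 trials per setting.

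| Odds ratio per factor | Type I, chi-square | Type I, adjusted | Power, chi-square | Power, adjusted | Gain (points) | Verdicts differ |
|---|---|---|---|---|---|---|
| 1.0 | 5.1% | 5.0% | 80.5% | 80.3% | −0.2 | 0.4% |
| 1.5 | 5.0% | 5.2% | 81.2% | 81.4% | +0.2 | 1.0% |
| 2.0 | 4.4% | 5.0% | 81.6% | 82.8% | +1.2 | 2.0% |
| 3.0 | 3.7% | 5.2% | 81.3% | 84.8% | +3.5 | 3.4% |

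The 6,000-trial run gave gains of −0.1, +0.4, +1.1 and +2.6 points, and chi-square type I errors of 3.9% at odds ratio 2 and 3.2% at odds ratio 3. A further run of 3,000 trials gave gains of 0, 1.0 and 3.3 points at odds ratios 1, 2 and 3, with verdicts differing in 0.5% to 4% of trials. The runs agree within simulation error on the pattern.

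**Step 4. Can the model be fitted?** Expected events are 199 × 0.20 + 199 × 0.10 = 59.7, about 60, for six parameters (intercept, treatment, four factors). That is about 10 events per parameter, which is adequate.

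**Step 5. Effect scale.** The design's 10% versus 20% corresponds to a marginal odds ratio of (0.10/0.90)/(0.20/0.80) = 0.44. A covariate-adjusted odds ratio is conditional on the factors and is a different quantity when they predict infection. A standardisation step is needed to return to the difference in percentages.

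**The case against.** The strongest reply is that the plan already contains the right model. Adjusted logistic regression is specified for the primary outcome, and adjusted Cox, logistic and linear models appear elsewhere, so the factors are not ignored. The natural reading is that the chi-square decides, since it is listed first and was used for sizing, and that the regression supports it. That is coherent. A formal label for the decisive analysis could also sit in a statistical analysis plan that is not shown. This stands to the extent that a missing label alone would not be a finding. What remains is the order the article does fix: the unadjusted test leads after a minimised allocation, when a better-matched analysis is already planned.

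Several stronger readings are tempting, and the document does not support them:

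- *The chi-square inflates false positives.* It does not. Its type I error is at or below 5% apart from simulation error; the issue is efficiency.
- *The four factors are known to be prognostic, so adjustment is free power.* The article gives no evidence on this. If they are not prognostic, the gain is nil; 3 points or so requires an odds ratio of about 3 for every one of the four factors.
- *Adjustment lifts power from 80% to 82–84%.* That uses the wrong baseline, as Step 2 shows.
- *The reported intervals will be too wide.* The article specifies no interval method. This follows only if a standard unadjusted interval is used and the factors are prognostic.
- *The risk difference is unavailable.* The crude difference comes straight from the two-by-two table; what is lacking is an adjusted one.

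**Conclusion.** The point holds as one of analysis choice, not validity. The leading test does not match the allocation method, and no rule says which of the two listed analyses decides. On the assumptions above, the cost of leaving it so ranges from nothing, if the factors do not predict infection, to about 1 point of power at an odds ratio of 2 per factor and about 3 points at 3. The chance that the two tests disagree rises over the same range from about 0.5% to about 4%. The required sample size is unaffected. Because the loss from adjusting is essentially nil even when the factors carry no information, the change is worth making despite the modest gain.

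The figures depend on assumed prevalences, independence, equal odds ratios and the biased-coin probability. They describe the Wald test on the log odds ratio; the interval for a standardised risk difference was not simulated.

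**What to change.** In the Statistical plan, or in the statistical analysis plan, and before outcomes are compared by arm:

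1. Name one primary analysis: logistic regression of infection (yes/no) on treatment and the four minimisation factors.
2. Report from that model the standardised (marginal) risk difference: the mean predicted risk over all analysed participants under mupirocin, minus the same under standard care, with a 95% CI. State how the interval is obtained (for example delta method or bootstrap), and which test from this model carries the conclusion.
3. Keep the unadjusted chi-square, with the crude percentages, as a sensitivity analysis.

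The existing sample size can stand; sizing on the chi-square is slightly cautious if the factors are prognostic.

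The cost is a few lines of wording and one extra standardisation step. The four factors are needed for allocation and so are already recorded at randomisation, and no further patients are required. If the factors turn out not to predict infection, nothing material is gained or lost.
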